### Secondary Outcomes Analyses

HCCQ scores will be compared similarly using a *t* test. Understanding ratings, which are on a scale from 1 to 5, will be compared using a Mann-Whitney *U* test for ordinal data or by dichotomizing responses as “understood well” for ratings of 4 or 5 and “not well” for ratings of 1-3, followed by a chi-square test. DDPRQ-10 scores, which yield a numeric difficulty score, will be compared by *t* test; additionally, we may compare the proportion of encounters meeting a “difficult” threshold (there is no absolute cutoff in literature, but >30 on the original 0-100 scale is sometimes used). Consultation time (in minutes) is likely to be skewed; we will compare medians with a Wilcoxon test, and also compare proportion of consultations exceeding a certain length (eg, >15 minutes) using a chi-square test.

We will consider *P*<.05 as significant for the primary outcome. For secondary outcomes, *P* values <.01 or <.05 will be interpreted with caution due to multiple comparisons. We are not formally adjusting for multiplicity, given that outcomes are correlated; however, the pattern of results will be considered collectively. Effect sizes will be presented (Cohen *d* for continuous outcomes, odds ratios for categorical comparisons) to gauge practical significance.

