**Results:**

Each trial targets 300 participants (150 per arm), providing greater than 80% power for an effect size *d*≈0.4 on the primary outcome (α=0.05). Outcomes are assessed immediately after the index consultation, with no additional follow-up planned in this protocol. We hypothesize that providing layperson-friendly summaries will significantly improve patients’ understanding and satisfaction with information, foster a more autonomy-supportive communication climate, and reduce physicians’ perceived difficulty in the encounter without unduly prolonging consultation time. Neither study received external funding. Both trials are currently in the recruitment phase, with patient enrollment scheduled to begin in May 2025 and expected to conclude by February 2026. Results are anticipated to be published in summer 2026.

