### Randomization and Blinding

Randomization was performed using a computer-generated randomization list created prior to study start. The list was produced with a validated random number generator, fully covering the planned sample size for each trial (n=300). Assignments were generated in a 1:1 ratio (intervention vs control) and exported into a password-protected file with time-stamp documentation. The randomization list was stored on a secure hospital server, accessible only to the principal investigator and the designated study statistician. Allocation concealment was maintained because recruiting staff and treating physicians had no access to the sequence; group assignment for each newly enrolled participant was revealed sequentially through a locked module at the point of inclusion. This procedure prevents prediction of future allocations while ensuring reproducibility and auditability.

Due to the nature of the intervention, blinding is not possible for participants or treating physicians. Patients in the intervention arm will receive an additional written summary that is clearly different from standard documents, and physicians will likely recognize if a patient has an easy-summary or not (eg, patients might refer to it during the consult). We considered having a blinded outcome assessor, but our outcomes are primarily self-reported by patients and the treating physician immediately after their encounter, so blinding is not applicable. The study analysts will remain blind to group labels until after data analysis (groups will be coded as A and B during statistical analysis to prevent subconscious bias). While lack of blinding may introduce some risk of bias, outcomes such as questionnaire scores are less prone to observer bias and more a reflection of the participant’s genuine experience. We will compare certain objective measures (like consultation length) to see if any Hawthorne effect (change in behavior due to being studied) is present similarly in both groups.

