For copyright and intellectual property reasons, the exact prompts cannot be disclosed. However, all prompts were version-controlled, and each version was archived with time-stamps in the study’s secure documentation system. Any changes in prompt wording or model parameters were logged and linked to the summaries generated during that phase. This ensures transparency and reproducibility of the process without requiring disclosure of proprietary content.

For outpatients (AI-INFOCARE), the summary is handed to them at the clinic check-in, so they can read it while waiting. For inpatients (AI-MEDTALK), the summary is given on the morning of discharge, a few hours before the formal discharge meeting with the physician. Patients are encouraged to read the summary and note any questions they have. They are told that this is “an explanation of your medical letter in simple language that you can keep.”

The physician conducting the consultation is aware that the patient has this summary (and in many cases, the physician will have seen it, since it mirrors the content of their own letter but in simpler form). However, physicians are instructed to conduct the consultation as they normally would, with no special training or script from the study. They will naturally address patient questions or clarify misunderstandings as needed. We will later examine whether having the summary changed the nature of questions patients ask or the flow of conversation (captured indirectly through outcomes such as consultation length and perception measures).

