#### Control (Usual Care)

Participants randomized to the control arm go through usual care procedures without any additional intervention. For outpatients, this means they have whatever documents they normally would (often patients do bring their referral letter or test results, but these are in technical language, and we do not provide any translated version). They will have their consultation with the doctor using those standard materials. For inpatients, usual care means they receive the standard discharge summary at the end of the discharge discussion (or sometimes given to them to hand to their next doctor), but not ahead of time in simplified form. Essentially, the control group represents the status quo: the patient relies on the doctor’s oral explanation during the consultation and on the standard medical documents, with no separate plain-language text.

All other aspects of care are identical between groups. Both groups’ consultations take place with the same pool of physicians (neurosurgery attendings or senior residents), in the same settings. Physicians will have the original medical documents in both cases for reference. After the consultation, both groups complete the outcome questionnaires described below.

Notably, if a patient in the control group expresses strong confusion about their medical documents or requests an explanation in writing, the physician will handle it per usual care (which might involve some oral explanation or writing brief notes, but the prepared AI summary will not be provided at that point, to preserve the integrity of the comparison). However, at the end of the study, control patients will be offered the layperson-friendly summary if they desire, as an ethical consideration to avoid denying potentially helpful information.

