#### Secondary Outcome 3: Physician’s Perception of the Encounter Difficulty

This outcome is measured by the Difficult Doctor–Patient Relationship Questionnaire, 10-item (DDPRQ-10) version [12]. The DDPRQ is a survey the doctor fills out after seeing a patient, reflecting how “difficult” or frustrating the physician found the encounter. It touches on feelings like “I found this patient difficult” or “This was a frustrating visit,” rated typically on a 6-point scale [13]. We are using the 10-item short form (each item 1=not at all, 6=a lot), which has been shown to retain high reliability (Cronbach α approximately 0.93) [12]. A total score is averaged (higher score means the doctor perceived the patient as more difficult). We chose this outcome to capture the physician’s side of the communication dynamic. Often, patients who are confused, anxious, or demanding due to lack of understanding can be perceived as “difficult” by doctors [13]. We hypothesize that doctors will rate encounters in the intervention arm as less difficult on average, since patients may be more at ease and focused on pertinent questions rather than expressing confusion or dissatisfaction. Each patient’s consulting physician will complete the DDPRQ-10 immediately after the consultation, before seeing the next patient, to ensure responses reflect that specific encounter.

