For physicians, one might worry that more informed patients could be more challenging, reflecting the stereotype of the patient arriving with a stack of internet printouts. However, research often contradicts this worry: physicians generally appreciate when patients have some baseline knowledge, provided it is accurate, because it can save time and lead to more focused questions [7]. Difficult physician–patient interactions often stem from misalignment of expectations or repeated explanation of basic issues [13]. We posit that our summaries will alleviate those factors, which is why we measure DDPRQ-10 to determine whether doctors find these conversations less frustrating or difficult. A reduction in “difficult” encounters is beneficial not only for patient care but also for physician well-being. Studies show that perceived difficult encounters correlate with physician burnout and suboptimal care [12]. If a simple intervention can reduce that strain, it represents a win–win. Of course, we must be cautious: it is possible that some doctors might feel the AI summary could undermine their role as information-giver or they might worry about inaccuracies. We have attempted to mitigate these concerns by involving physicians in validating the summaries and making clear that the tool is an aid, not a replacement for their explanations.

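### The DDPRQ-10 t test ignores the rating physician: it wastes precision, and it gives too narrow an interval for physicians in general if they react differently to the summary

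*Protocol article*

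**What the plan says.** The DDPRQ-10 is the only outcome rated by physicians. Under Secondary Outcome 3, each patient's "consulting physician will complete the DDPRQ-10 immediately after the consultation, before seeing the next patient". Under Control (Usual Care), consultations in both groups "take place with the same pool of physicians (neurosurgery attendings or senior residents), in the same settings". The number of physicians is not given.

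Randomization and Blinding states that "blinding is not possible for participants or treating physicians", and the intervention section adds: "The physician conducting the consultation is aware that the patient has this summary". That section describes allocation as 1:1 from a computer-generated list and mentions no stratification by physician.

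Secondary Outcomes Analyses fixes the test: "DDPRQ-10 scores, which yield a numeric difficulty score, will be compared by" a *t* test. It names no physician term.

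Two other places bear on physicians:
- The bias safeguards in Randomization and Blinding promise sensitivity analyses adjusted for age, education and clinician identifier, without saying for which outcomes.
- Subgroup and Exploratory Analyses will explore whether the effect differs by doctor, possibly with interaction terms. The worked example there is for FAPI and health literacy.

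**The concern.** The 300 scores per trial are repeated ratings by a shared set of raters who know which patients had the summary. Two things can follow.

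First, physicians may differ in how harshly they rate. A test that ignores this leaves the variation in the error term.

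Second, physicians may differ in how they respond to the summary. The Discussion raises this itself: "some doctors might feel the AI summary could undermine their role as information-giver". The subsection on consultation dynamics again allows that a doctor may react unexpectedly. In that case the average effect depends on which physicians happened to take part, and a *t* test on patients does not count that uncertainty.

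The abstract's hypothesis includes a reduction in physicians' "perceived difficulty in the encounter without unduly prolonging consultation time". The Discussion connects fewer difficult encounters with physician well-being, and positive trial results with wider implementation. With few raters, one or two enthusiasts could produce a significant difference that does not describe physicians elsewhere.

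**Working it through.** **Stated figures, with independent observations.**
- FAPI: difference 0.5, SD 1.0, 80% power, two-sided 0.05. n = 2(1.96 + 0.842)²/0.5² = 62.8, so 63 per group. This matches the protocol.
- DDPRQ-10: the protocol claims more than 80% power for 10 points on a 0-100 scale and gives no SD. With 150 per arm, 80% power needs d = 0.3245, so the claim holds for any SD up to 10/0.3245 = 30.8 points, if ratings are independent.

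**Inputs for the check.** From the protocol: 300 patients, 150 per arm, individual 1:1 allocation, physicians crossed with arms. Assumed, because the protocol gives none of them: the number of physicians J, the share of variance due to rating level (ICC), and the SD of the arm effect between physicians (tau, in DDPRQ-10 SD units). Total variance is set to 1.

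**Step 1: rating level only (tau = 0).** The *t* test has variance 2/150 = 0.01333, SE 0.1155. Simulated type I error at ICC 0.2 is 4.4-4.9%, and 3.3% (conservative) if arms are balanced within physician. So validity is not at issue here. Precision is:
- Without a physician term, power at d = 0.3: Φ(0.3/0.1155 − 1.96) = Φ(0.64) = 74%.
- With a physician term at ICC 0.3, ignoring chance imbalance: SE = √(2 × 0.7/150) = 0.0966, and Φ(0.3/0.0966 − 1.96) = Φ(1.15) = 87%.
- Simulation, with chance imbalance within physicians: 72-76% without and 83-86% with the term at ICC 0.3; 74% and 75-78% at ICC 0.1.

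**Step 2: the arm effect also varies.** For inference to physicians in general:

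Var(difference) = tau²/J + 2(1 − tau²/4)/150

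- J = 10, tau = 0.2: 0.0040 + 0.0132 = 0.0172. SE ratio to the *t* test = √(0.0172/0.01333) = 1.14. Type I error = 2[1 − Φ(1.96/1.14)] = 8.4%.
- J = 10, tau = 0.3: 0.0090 + 0.01303 = 0.02203. SE 0.148 instead of 0.1155, ratio 1.29, type I error 12.7%.
- J = 10, tau = 0.1: 5.8%. J = 20, tau = 0.1: 5.4%. J = 30, tau = 0.1: 5.3%.
- J = 5, tau = 0.3: ratio 1.53, about 20%.

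**Step 3: simulation.** ICC 0.2, 3,000 runs per row; type I error at nominal 5%:

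| Physicians | tau | *t* test | Clinician as main effect | Within-physician differences |
|---|---|---|---|---|
| 6 | 0 | 4.9% | 5.2% | 4.4% |
| 6 | 0.2 | 11.7% | 12.7% | 5.5% |
| 6 | 0.3 | 18.3% | 19.7% | 4.7% |
| 10 | 0 | 4.5% | 5.3% | 4.6% |
| 10 | 0.2 | 9.0% | 8.8% | 4.9% |
| 10 | 0.3 | 12.6% | 14.0% | 4.6% |
| 20 | 0 | 4.4% | 4.7% | 4.8% |
| 20 | 0.2 | 6.9% | 6.9% | 4.9% |
| 20 | 0.3 | 7.6% | 8.2% | 3.5% |

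The clinician main effect, the form planned as a sensitivity analysis, removes level differences but leaves the inflation in place. A one-sample test on the within-physician differences stays near 5%.

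**Step 4: price of that test.** With 8-12 physicians, its power at d = 0.3 is 63-66% against 74% for the *t* test at ICC 0.1, 75-77% against 74-76% at ICC 0.3, and 87-89% against 76-78% at ICC 0.5.

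**The case against.** A reader might infer that 300 ratings from a few physicians make the *t* test invalid outright. The documents do not support that. Individual randomization with physicians in both arms keeps the test at its nominal level when physicians differ only in how they rate. Nor does the protocol say that the pool is small.

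The other side has more to say:
- **Scope of the hypothesis.** Secondary Outcome 3 speaks of doctors' average ratings in the intervention arm, which can be read as an average over this trial's encounters. For that target the *t*-test interval is not too narrow. This stands, and it is why the second part of the point is conditional on generalizing.
- **Differing reactions are only possible.** The Discussion predicts no size. It says physicians generally appreciate informed patients and describes steps to ease concerns. This stands; tau is an assumption.
- **The by-doctor analysis.** Subgroup and Exploratory Analyses would look for exactly this pattern. But it is exploratory, its example is FAPI, and it does not alter the reported DDPRQ-10 interval.
- **Caution on secondary outcomes.** It is promised, but for multiplicity, not for shared raters.
- **SAP territory.** Random-effects detail is commonly left to the SAP, which is not shown. However, the protocol does fix a test here, and it is one without a physician term.
- **Power.** Making the physician-level test the only analysis would lose power at low ICC. This stands, so it belongs in a supporting role.

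**Conclusion.** The point holds in a limited form. The DDPRQ-10 test leaves out a rater effect that the design makes obvious and that the planned clinician identifier could supply. The definite cost is precision: about 10 percentage points of power at d = 0.3 if the ICC is 0.3, and little if it is 0.1.

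The conditional cost is a too narrow interval for physicians in general. It runs from negligible (about 5.3-5.4% type I error with 20-30 physicians and tau 0.1) through about 8-14% (10 physicians, tau 0.2-0.3) to about 20% (5 physicians, tau 0.3). All of these sizes rest on an assumed number of physicians and an assumed tau; the simulated and power figures also rest on an assumed ICC. For a conclusion limited to the participating physicians, the *t*-test interval is not too narrow. The primary FAPI conclusion is not affected by this point.

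**What to change.** In Secondary Outcomes Analyses:
1. Make the main DDPRQ-10 analysis a linear model for arm with a random physician intercept, using the clinician identifier already planned for the sensitivity analyses.
2. Report how many physicians rated, and show the arm difference for each physician by code.
3. Add a supporting analysis that lets the effect vary by physician: a random physician-by-arm effect with small-sample degrees of freedom, or a test of the mean within-physician difference.
4. State that, unless the supporting analysis agrees, the DDPRQ-10 conclusion is limited to the participating physicians.

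The cost is wording, with no new data. The physician intercept has no type I cost when physicians react alike. The supporting analysis has a wider interval and less power if rating levels differ little (63-66% against 74% at ICC 0.1), which is why it should not replace the main analysis.

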### Subgroup and Exploratory Analyses

We plan to explore whether the effect of the intervention differs by subgroups such as age, with older patients potentially benefitting more or less, education level, with those having lower education or health literacy possibly gaining more, and by doctor. To do this, we may run an ANOVA or regression with interaction terms. For example, we will use a linear regression with FAPI score as the outcome, the intervention as predictor, and an interaction term between intervention and health literacy level, if available from a brief screening question, to examine whether the effect varies. These analyses are exploratory and hypothesis-generating.

We will also analyze the results of the two trials side by side to see whether context, specifically outpatient versus inpatient, influences outcomes. If the direction and magnitude of effect are similar across trials, this strengthens generalizability. If one trial shows a different outcome, for instance if in one context the summary is more beneficial, that will be an interesting finding to explore qualitatively.

All analyses will be performed using SPSS (version 28; IBM Corp) and R software (R Foundation for Statistical Computing). Data analysis will commence after all follow-up is complete. No interim analysis for early stopping is planned, as the intervention is low-risk.

## Results

As of May 2025, the trials are in the prerecruitment phase. All regulatory approvals and registrations are in place. Recruitment will commence on May 26, 2025, and is expected to continue until February 2026 or until the target sample sizes are reached. Statistical analysis plans have been finalized prior to trial initiation. Data analysis is expected to begin promptly after completion of data collection. Results are anticipated to be published in summer 2026. Neither study received external funding.

To date, no participants have been enrolled and no interim data are available; therefore, we cannot report any baseline characteristics or outcomes. Enrollment rates will be monitored closely. Based on clinic volumes, we anticipate enrolling approximately 50 outpatients and 25 to 30 inpatients per month, which should allow reaching 300 in each trial within 6 months. If necessary, recruitment may be extended or involve additional centers, but at this time the plan is to keep it single-center and within the 6-month window.

Each trial’s progress and any protocol deviations will be documented. An independent data safety officer will periodically review recruitment and any AEs. We do not expect any physical AEs from this type of intervention. Potential adverse outcomes could include a patient being very upset by understanding their diagnosis; ethically, such reactions are part of informed care. Physicians will manage these situations with appropriate counseling. No such cases have occurred to date, as the trials have not yet started.

We will publish the trial results in a peer-reviewed journal upon completion and also plan to share findings with stakeholders, including patient advocacy groups and the hospital administration for potential implementation. The trial registration details, DRKS00036810 for AI-INFOCARE and DRKS00036814 for AI-MEDTALK, are publicly accessible, and we will update those entries with a results summary after study completion as required by guidelines.

In summary, at this protocol publication stage, we confirm that everything is ready for execution of the trials. The key upcoming milestone will be the enrollment of the first patient, anticipated in late May 2025. We will treat the first few cases as a pilot to ensure logistics, such as timely generation of the AI summary while the patient is waiting, function smoothly, then proceed to full recruitment.

We will present the final analyzed results, including comparisons between the intervention and control group for all outcomes, after the trial is completed. These results will allow us to evaluate our hypotheses on whether AI-driven simplification of medical documents can measurably improve the doctor–patient communication experience.

In addition to peer-reviewed publication, results, whether positive or negative, will be posted on the Deutsches Register Klinischer Studien registry, summarized in patient-readable German on the hospital website, and shared with patient advocacy groups and professional societies. Appendices including standard operating procedures and fidelity metrics, will be made available where feasible.

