### Study Design and Setting

Both AI-INFOCARE and AI-MEDTALK are designed as prospective, parallel-group RCTs. The trials share a common overall design, with nearly identical interventions and outcomes, but target different patient populations and phases of care (outpatient pretreatment vs inpatient discharge). The study setting is the Department of Neurosurgery at University Hospital Carl Gustav Carus, Technische Universität Dresden, Germany, which includes outpatient clinics and inpatient wards. The trials are investigator-initiated collaborations between the hospital and Simply Onno GmbH (Berlin; [9]), a health AI startup.

The overall structure of the trials is summarized in Figure 1. Each trial will enroll participants over a 6-month recruitment period and follow a simple two-arm randomized design (intervention vs control). There is no blinding (open-label) and no crossover between arms. Outcome assessments are conducted at a single postintervention time point (immediately after the index doctor–patient consultation during which the intervention could have an effect). There are no long-term follow-ups in this protocol, as the primary focus is on the immediate communication outcomes of the consultation.

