### Participants and Recruitment

Each trial will recruit approximately 300 patients (150 per arm), for a total of 600 participants across both trials. Participants will be recruited consecutively from the patient population served by the neurosurgery clinic. AI-INFOCARE will enroll ambulatory patients before a planned treatment, and AI-MEDTALK will enroll hospitalized patients at discharge after surgery.

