### Sample Size and Power Calculation

We determined the target sample size of 300 patients per trial (150 per arm) through power analysis based on the primary outcome (FAPI score). From previous studies using the FAPI/QQPPI in similar settings, we estimate the mean (SD) FAPI score in usual care to be approximately 3.5 (SD 1.0) on the 5-point scale. We consider an increase of 0.3-0.5 in the mean score (with 0.5 being a medium effect, roughly half an SD) to be a clinically important improvement in communication quality. To detect a difference of 0.5 with 80% power at a 2-sided α of 0.05 using a 2-sample *t* test (2-tailed), approximately 63 patients per group are required. To be conservative and account for potential dropout or non-evaluable responses (eg, incomplete questionnaires), we inflated the sample. Our goal of 300 participants per trial (150 per arm) provides >90% power to detect an effect size of *d*=0.5 and approximately 80% power to detect a smaller effect of *d*≈0.4. This sample also provides ample power (>80%) for detecting differences in secondary outcomes, such as a 10-point difference in the 0-100 scaled DDPRQ-10 or approximately a 1-point difference in the understanding rating. We do not plan an interim efficacy analysis, but an internal check of assumptions, such as variance, will be conducted after approximately 50% enrollment to ensure the sample size remains adequate. Given the consecutive recruitment strategy, we anticipate reaching 300 patients in each trial within the planned 6-month recruitment window, as the neurosurgery service sees dozens of new patients weekly and discharges dozens monthly, with a good proportion expected to consent.

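### At the article's own rate of 25 to 30 inpatients a month, AI-MEDTALK reaches 150 to 180 patients in 6 months and about 206 to 274 by February 2026, not 300

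*Protocol article*

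**What the plan says.** The article sets a target of about 300 patients (150 per arm) for each of the two trials (Participants and Recruitment). It describes the recruitment time in two ways.

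- **Six months for each trial.** Study Design and Setting: "Each trial will enroll participants over a 6-month recruitment period". Sample Size and Power Calculation: "we anticipate reaching 300 patients in each trial within the planned 6-month recruitment window". Results: "50 outpatients and 25 to 30 inpatients per month, which should allow reaching 300 in each trial within 6 months".
- **A calendar end.** Results: "Recruitment will commence on May 26, 2025, and is expected to continue until February 2026 or until the target sample sizes are reached". The Abstract also gives May 2025 to February 2026.

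The Results section allows that recruitment may be extended or other centers added if needed, but then says "at this time the plan is to keep it single-center and within the 6-month window". It anticipates publication in summer 2026, as does the Abstract.

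Power is attached to 150 per arm. The Sample Size section states more than 90% at d=0.5 and approximately 80% at d of about 0.4. The Abstract states more than 80% at d of about 0.4. The section Two Trials Versus One says that each trial is powered on its own.

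**The concern.** The accrual sentence draws one conclusion for both trials from two very different monthly rates. The inpatient rate is 50 to 60% of the outpatient rate, yet both trials are said to reach the same total in the same time. The 6-month window appears in three sections, so this is not a single slip.

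What is at stake is which statement gives way when the shortfall appears. If the 6-month window is kept, AI-MEDTALK ends at about half to 60% of its size and loses the power stated for it. If the target is kept, both stated time frames are exceeded and the summer 2026 results date becomes tight, because analysis starts only after data collection is complete.

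The article also plans to set the two trials side by side and to read a difference between them as an effect of context. If AI-MEDTALK were much the smaller trial, a non-significant result there could reflect size alone.

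**Working it through.** **Inputs (all from the article).** Target 300 per trial, allocated 1:1. Accrual of 50 outpatients and 25 to 30 inpatients a month. Window of 6 months, or 26 May 2025 to February 2026. SD 1.0, two-sided α 0.05, two-sample t test, d of 0.4 and 0.5. No dropout rate is given, so every enrolled patient is taken as evaluable.

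**1. Accrual = rate × months, over 6 months**
- AI-INFOCARE: 50 × 6 = 300. The stated figure reproduces, with no slack.
- AI-MEDTALK: 25 × 6 = 150 and 30 × 6 = 180. The stated 300 does not reproduce. The shortfall is 120 to 150 patients (40 to 50%).

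**2. Accrual to February 2026**
- From 26 May 2025 to 1 February 2026 is 8.25 months: 25 × 8.25 ≈ 206 and 30 × 8.25 ≈ 247.
- From 26 May 2025 to 28 February 2026 is 9.13 months: 25 × 9.13 ≈ 228 and 30 × 9.13 ≈ 274.
- The range is therefore about 206 to 274, or 103 to 137 per arm.

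**3. Time and rate needed for 300 inpatients**
- 300/30 = 10 months (late March 2026); 300/25 = 12 months (late May 2026).
- To finish in 6 months: 300/6 = 50 a month. To finish in February: 300/9.13 to 300/8.25, or about 33 to 36 a month.

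**4. The article's own sample size figures**
- n per group at d=0.5 and 80% power: 2 × (1.960 + 0.842)² / 0.5² = 62.8, so 63. This reproduces (64 by the exact t).
- At 150 per arm, power is 99% at d=0.5, consistent with the stated more than 90%. At d=0.4 it is 93%, so the Abstract's more than 80% is true as a bound, and the Sample Size section's approximately 80% understates it.
- 80% power at d=0.4 needs about 100 per arm.

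**5. Power if AI-MEDTALK stopped early**

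Noncentral t with 2n − 2 degrees of freedom and noncentrality d × √(n/2). As a check at n=75, d=0.4: 0.4 × √37.5 = 2.449, and the normal approximation Φ(2.449 − 1.960) gives 69%, against 68% exact.

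| Closing | n per arm | d=0.4 | d=0.5 |
|---|---|---|---|
| 6 months, 25 a month | 75 | 68% | 86% |
| 6 months, 30 a month | 90 | 76% | 92% |
| 1 February 2026, 25 a month | 103 | 82% | 95% |
| 28 February 2026, 30 a month | 137 | 91% | 98% |
| Target reached | 150 | 93% | 99% |

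A 6-month stop misses the stated power at d=0.4 across the whole range, and misses more than 90% at d=0.5 at the lower rate. A February close meets every stated power figure before dropout. At the lowest February figure the margin is thin: 103 against about 100 evaluable patients per arm.

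**The case against.** The strongest reply is that power belongs to 150 per arm and not to a window. The article foresees a longer recruitment or more centers, says enrollment will be monitored closely, and names reaching the target as one of the two ends of recruitment. On that reading AI-MEDTALK still gets its 300 patients, and only a forecast was too optimistic. This stands as far as power is concerned. It does not rescue the forecast, because with 300 kept at one center both stated time frames fail.

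A reader might infer more than the article supports, in four ways.

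- **That AI-MEDTALK is underpowered as planned.** Only a stop at 6 months falls below the stated power. A February close does not, before dropout. Even at 6 months, each arm exceeds the 63 on which the basic calculation rests.
- **That an extension is certain.** The article also names additional centers. What follows from its figures is that the single-center, 6-month plan fails at the stated rate.
- **That the February date would end the trial short.** The wording is "expected to continue until February 2026 or until the target sample sizes are reached". This is an expectation with two alternative ends and no order between them. It is ambiguous, not a fixed stopping rule.
- **That a longer recruitment would harm the test.** No interim efficacy analysis is planned, and analysis follows complete data collection. Recruiting on to the planned 300 would not in itself inflate the type I error.

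**Conclusion.** The point holds as an internal contradiction. At 25 to 30 inpatients a month, AI-MEDTALK enrolls 150 to 180 patients in the stated 6 months and about 206 to 274 by February 2026. Reaching 300 at one center takes 10 to 12 months. The rate, target, 6-month window and February date cannot all be true for this trial, and the two time frames also disagree with each other (6 months against about 8.2 to 9.1).

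The loss of power is conditional: clear after a 6-month stop, absent on the stated figures after a February close, and nil at 300. These results assume steady accrual at the stated rate from 26 May 2025 and complete outcome data. Any dropout lowers the power figures.

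Severity is moderate. The planning figures are wrong for one of two trials and should be corrected, but the effect estimate and the primary test are not biased.

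**What to change.** Choose one of two routes for AI-MEDTALK and state it.

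- **Keep 300.** Give this trial its own window that matches its rate: 10 to 12 months at a single center, or the additional-centers option that the Results section already mentions, with the combined monthly rate then expected.
- **Keep a fixed closing date.** Restate the expected size and the power for this trial: about 206 to 274 patients and 82 to 91% at d=0.4 for a February 2026 close, with an allowance for dropout.

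In either case, say for each trial whether the date or the target of 300 governs closing. Then align the Abstract, Study Design and Setting, Sample Size and Power Calculation, and Results, including the date on which AI-MEDTALK results are expected. The 93% power at d=0.4 with 150 per arm can be corrected in the same edit. The registry record was not available here, so check whether it carries the same dates.

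The cost is wording, plus either a longer inpatient timeline or a less favorable stated size and power. No patients are needed beyond those already planned.
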